### Data collection methods, respondents and sample size

i.Key informants’ interviews (KIs)

A total of 30 KIs selected based on their knowledge, position and experience on WASH aspects in HCFs will be conducted. KIs will include supervisors/managers of HC IIIs and IVs, nurses, administrators, Environmental Health Officers as well as officials from the MOH and district health office. KIs interviews will be used to explore the barriers and facilitators of hand hygiene in HCFs, and this will be done using a KIs’ interview guide, which is provided in Additional file 2.
ii.Semi-structured interviews

A total of 30 semi-structured interviews with HCF managers will be conducted, to assess barriers and facilitators to hand hygiene, motives of hand hygiene, social norms related to hand hygiene, behavioural settings and touch points. This will be done using a semi-structured interview guide provided in Additional file 3.
iii.Structured observations in HCFs

As part of the formative study, observations using a structured observation checklist (Additional file 4) will be conducted in 100 HCFs to assess the hand hygiene infrastructure, roles, presence of hand hygiene supplies, functionality of facilitates, and norms in maternity and children’s wards.
iv.Cluster randomized trial

A sample size of 30 clusters [HC IIIs and IVs] (15 HCFs under the intervention and 15 HCFs under the control arm) with 15 HCWs per HCF will allow us to detect a 20% increase in the proportion of HCWs that practice hand hygiene (hand washing/hand rub) at the 5 critical moments at 4 months between the control and the intervention groups. The calculation of the sample size is based on the following assumptions: a 25% and 5% increase in hand hygiene in intervention and control group respectively, a standard normal deviate of at 95% confidence level (1.96), a standard normal deviate at 80% power level (0.84), the proportion of HCWs practising hand hygiene in the control group (0.747) from an infection control study in HCFs in Arua district, Northern Uganda [39] and a design effect of 2.0 to account for the fact that there would be clustering of HCWs within HCFs. This gives a sample size of 426, however, in order to achieve a consistent cluster size, the sample size will be rounded off to 450 HCWs participants, with 225 in each of the study arms. The study will recruit 450 HCWs (doctors, clinical officers, nurses and midwives) who work in maternity and children’s wards. In each HCF, the study will target 13 nurses/midwives and 2 Doctors/Clinical Officers.

### Evaluation

We shall conduct process and outcome evaluations. The process evaluation will be conducted at the midline to understand how the intervention has been implemented. The process evaluation will seek to establish: whether the intervention is being implemented according to plan; whether the intervention is working or not; how many HCWs will be getting exposed to the touch points; how many HCWs will be responding to the mhealth intervention as well as the aspects of the intervention that participants will have liked. The baseline, midline and end-line evaluations will be conducted using a tool provided as Additional file 5.

To assess the outcome of the intervention, a structured questionnaire will be administered at baseline, midline (2 months after starting intervention) and end-line (4 months) as indicated the participants’ timeline in Fig. 2. During surveys, social demographic, knowledge and attitudes questions will be collected from all participating HCWs through an interviewer administered questionnaire. The questionnaires will be administered to the HCWs before the hand hygiene observations. In order to maintain systematic consistency for measurement indicators, the same research tools used at baseline will be used for mid-term, end-line and impact evaluation. In addition, observations of hand hygiene practice among the HCWs will be done at baseline, midline and end-line using an observation tool. Hand rinsates will be collected and analysed, and the results will be entered in a hand rinsates form. All the data collection tools to be employed will be guided by the WHO’s 5 moments for hand hygiene [37].

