### Outcome measurement

The primary outcome will be the proportion of utilized hand hygiene opportunities (number of critical times hand hygiene is observed to be done with soap and water or ABHR) out of the total number of observed hand hygiene opportunities. The secondary outcome will be *E. coli* concentration levels in hand rinsates from HCWs, which indicates recent fecal contamination and hand hygiene failure.

We shall determine the two outcome variables using two approaches. Firstly, observations based on the WHO’s 5 moments for hand hygiene which include: before touching a patient; immediately before performing an aseptic procedure; immediately after an exposure risk to body fluids (and after glove removal); after touching a patient and his or her immediate surroundings when leaving as well as after touching any object or furniture in the patient’s immediate surroundings, when leaving - even without touching the patient [37]. Hand hygiene observations will be conducted during the baseline, midline and end-line surveys. The hand hygiene observations will be done in the mornings (8 am – 12 pm) and evenings (4 pm – 8 pm) since these are considered to be peak treatment hours [36]. Within the targeted time, 20 hand hygiene opportunities will be observed for each of the selected HCWs (corresponding to 10 patients each with 2 hand hygiene opportunities, which will include before touching a patient and after touching a patient), and the used and missed opportunities will be recorded. Therefore, a total of 9000 hand hygiene opportunities will be observed by experienced researchers (HCWs or environmental health officers), who will observe from the least obtrusive point within a radius of 5–10 m of the patient wards [38].

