### Strengths and limitations of the study

To the best of our knowledge, this may be the first study to evaluate the impact of environmental cues and mhealth on hand hygiene practice among HCWs. However, observations of hand hygiene practice among HCWs are likely to be affected by social desirability bias. To solve this challenge, RAs that will undertake the observations will be trained, standard WHO observation tools will be used, and where possible two observers will be used to observe hand hygiene behaviour simultaneously. In addition, our findings are likely to be influenced by a change in hand washing behaviour, which could be attributed to the recent COVID-19 pandemic. The effect of COVID-19 will be factored in during data analysis through stratification of data.

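### At every survey round the knowledge-and-attitudes interview comes before the hand hygiene observation, so it may prompt the behaviour that the primary outcome measures

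*Protocol article*

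**What the plan says.** The Evaluation section schedules a structured questionnaire at baseline, at midline (2 months) and at end-line (4 months). On content and mode it says that "social demographic, knowledge and attitudes questions will be collected from all participating HCWs through an interviewer administered questionnaire". On order it says "The questionnaires will be administered to the HCWs before the hand hygiene observations". It adds that "All the data collection tools to be employed will be guided by the WHO’s 5 moments for hand hygiene", and that "the same research tools used at baseline will be used for mid-term, end-line and impact evaluation", so the sequence repeats unchanged at each round.

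Outcome measurement defines what follows the interview: "The primary outcome will be the proportion of utilized hand hygiene opportunities", scored by direct observation within the same three survey rounds. Hand rinsates for *E. coli*, the secondary outcome, are taken immediately after the observations, so they too come after the interview.

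Strengths and limitations concedes that "observations of hand hygiene practice among HCWs are likely to be affected by social desirability bias". The remedies given there are observer training, standard WHO observation tools and, where possible, two simultaneous observers. No section gives a reason for putting the questionnaire first or sets an interval between it and the observation.

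**The concern.** The trial tests whether reminders change hand hygiene. The Discussion expects the text messages to work by reminding HCWs to clean their hands at the critical moments of care. Under Trial interventions, the message content is the benefits of hand hygiene and when and how to do it. An interview on knowledge and attitudes, built on the 5 moments, is plausibly a cue of the same kind. It is given to every HCW, control arm included, before that HCW is scored.

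Three things are at stake:

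- Observed compliance may be inflated in both arms.
- The baseline may not describe routine practice, which weakens the before-and-after comparisons listed in Table 3.
- The contrast between arms may be diluted, because control HCWs receive a reminder-like cue at each measurement.

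The protocol sees reactivity as a threat, but its remedies concern how behaviour is recorded. None concerns an interview that may change the behaviour first.

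**Working it through.** **Order of events.** From Evaluation and Outcome measurement, each round runs: interview, then observation (primary outcome), then hand rinsate where one is taken (secondary outcome). Both named outcomes come after the interview. The questionnaire supplies neither of them.

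**Inputs for an illustration** (Data collection methods, Cluster randomized trial): control proportion 0.747; rises of 5% (control) and 25% (intervention); 1.96 and 0.84; design effect 2.0; 225 HCWs per arm. The text does not say whether the rises are relative or absolute. I use the relative reading:

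- control 0.747 × 1.05 = 0.784
- intervention 0.747 × 1.25 = 0.934

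**The plan's own figure.** With the pooled two-proportion formula, 0.784 vs 0.934 needs 84 per arm, so 84 × 2 arms × 2.0 = 336, or 388 with a continuity correction. The absolute reading (0.797 vs 0.997) gives 144, or 180 corrected. The stated 426 is not reproduced. That is a separate matter, and nothing below depends on it.

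**Power formula.** Effective n per arm = 225 / 2.0 = 112.5. With d the difference and p̄ the mean proportion:

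- SE0 = √[2 p̄(1 − p̄)/112.5]
- SE1 = √{[p1(1 − p1) + p2(1 − p2)]/112.5}
- power = Φ[(d − 1.96 × SE0)/SE1]

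No priming: p̄ = 0.859, SE0 = 0.0464, SE1 = 0.0453, so power = Φ[(0.150 − 0.0909)/0.0453] = 90%.

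**Scenario A (assumption):** priming removes a fraction f of missed opportunities in both arms, so each p becomes 1 − (1 − p)(1 − f).

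| f | control | intervention | difference | power |
|---|---|---|---|---|
| 0 | 0.784 | 0.934 | 0.150 | 90% |
| 0.2 | 0.827 | 0.947 | 0.120 | 82% |
| 0.3 | 0.849 | 0.954 | 0.105 | 75% to 76% |
| 0.5 | 0.892 | 0.967 | 0.075 | 60% |

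**Scenario B (assumption):** only control rises, by 5 points, giving 0.834 vs 0.934. SE0 = 0.0427 and SE1 = 0.0422, so power = Φ[(0.100 − 0.0837)/0.0422] = 65%.

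The result depends on the starting values. With 0.747 vs 0.947, scenario A at f = 0.5 still leaves 81% power (99% without priming), and scenario B leaves 93%.

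**The case against.** **Both arms are interviewed alike.** This stands: the procedure favours neither arm by design. A reader might infer that control HCWs are lifted most because they get no other reminders. The documents do not support that. Both arms also receive hand hygiene facilities where needed, soap, alcohol rub at points of care and a demonstration at the start. HCWs already prompted by messages could respond to the interview as much or more. The sign of any interaction is unknown.

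**Only the order is stated, not the gap.** This also stands. Observations run in morning and evening windows, and the gap could be minutes or days. The timeline figure and the evaluation tool (Additional file 5) are not available here. That the knowledge and attitude items concern hand hygiene is a fair inference from the sentence on the 5 moments, but the items themselves cannot be seen.

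**The loss of power can be overstated.** A reader might take the standard error implied by 80% power for 20 points, 20/2.8 = 7.14 points, and conclude that power for 15 points is Φ(15/7.14 − 1.96) = 56%. That is not valid. With 112.5 effective HCWs per arm, the standard error cannot exceed √(2 × 0.25/112.5) = 6.67 points at any pair of proportions. At 84.7% vs 99.7% it is about 3.4 points and power is about 99%.

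**Headroom is a separate matter.** On the absolute reading, control reaches 79.7%, leaving 20.3 points for a 20-point target. That limit comes from the sample-size assumptions whatever the order of measurement. It would not bind at the 15% adherence cited in the Discussion.

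**Reversal cannot remove all reactivity.** True. HCWs are told the study's purpose at consent, and observers stand within 5–10 m. The baseline interview would also still precede the later rounds, though by months.

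**Conclusion.** The point holds as a sequencing weakness that is stated in the text and can be avoided. The interview precedes both named outcomes at every round at which they are measured, no reason is given, and the listed remedies do not address it. The supported consequences are possible inflation of compliance in both arms, a baseline that may not reflect usual practice, and possible dilution of the contrast.

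The size is not known. The illustrated fall from about 90% to between 82% and 60%, or to 65%, rests on assumed priming effects, on the relative reading of the 5% and 25% rises, and on the plan's simplification to one binary result per HCW with a design effect of 2. It shows what a moderate effect could do and does not estimate the loss. The documents do not show a bias towards either arm, a fixed power deficit, or that the interview takes place immediately before scoring.

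**What to change.** At all three rounds, specify the sequence as: consent (at enrolment) and identification of the HCW; observation; hand rinsate at the rounds where one is taken; then the questionnaire. Replace the sentence on order in Evaluation and make the same change in the field manual. Also state in Strengths and limitations that reactivity from consent and visible observers remains.

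Visits, tools, staff and sample size do not change. The one drawback is that questionnaire answers may be slightly coloured by having just been observed. They are neither the primary nor the secondary outcome, so this is the better place to accept some reactivity. If the order cannot be changed for practical reasons, give the reason, fix a minimum interval between interview and observation that is the same in both arms, and record the actual interval for each HCW.

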**Fig. 2 Fig2:**
[figure not shown]
Project phases and timing

### Data management and analysis plan

#### Data management

Data will be collected electronically using tablets or phones preloaded with Open Data Kit software. Data capture forms with in-built restrictions plus logical checks to minimize errors and missing data at collection will be designed by the study data management team. The data collected from the field will be submitted to the cloud server on a daily basis, and only accessible by the data management team for data security purposes. The data will be downloaded in a comma-separated value (csv) format, and then exported to STATA version 14 after which consistency checks programs will be run daily and error reports produced. The generated errors will be sent back to the field team for clarification and cleaning. The data manager will be responsible for the security of the data and will back it up on the cloud server on a daily basis to avoid its loss.

Study progress will be monitored by comparing numbers accrued against those expected. Numbers accrued will further be verified against the physical counts from the field team. Progress reports will be provided to the study team on a daily basis for purposes of monitoring the progress. There will be a data quality team which will monitor the data collection activity and carry out re-interviews on a randomly selected percentage of the records to further ensure quality data is collected. Data will be treated as confidential by the study personnel and all records will be kept secure in locked filling cabinets and offices will be treated with utmost confidentiality.

#### Data analysis

i.Qualitative analysis (formative stage)

The KIIs will be transcribed verbatim by two experienced transcribers. The typed transcripts will then be read several times by all members of the study team who will then develop codes. Code book definitions will be based on the objectives of the study while integrating in emerging themes from the data. The code book will be discussed and agreed upon by the study team. Then two experienced research assistants (RAs) will code the articles using ALTAS-ti software to ease further analysis. The code reports will then be read and discussed by all the investigators who will agree on both codes and categories. Then, codes will be grouped into categories, themes and subthemes [40].
ii.Quantitative analysis (effect of intervention)

The effect of the intervention will be evaluated at two time-points: midway the intervention, and immediately after the completion of the intervention period to assess the short-term effects on hand hygiene. Data from all surveys will be double entered into Open Data Kit (ODK) collect, and statistical analysis will be carried out using Stata version 14. We will calculate the prevalence of cluster level hand hygiene at baseline and follow-up for each HCF. Mixed sub-group analysis will be stratified by sex, cadre, experience, and level of training. We shall run multivariable logistic regression under the generalised estimating equations (GEE) framework to account for the dependence of hand hygiene on the intervention in a marginal way. This approach will give population average estimates for effect of intervention while accounting for other covariates in the model. An exchangeable correlation structure will be considered. Table 3 provides a summary of the study objectives, methods and data analysis procedures.

**Table 3 Tab3:** Summary of study objectives, methods and data analysis procedures

Objectives	Study population	Data collection methods	Indicators	Data analysis
Explore the facilitators for enhancing healthcare workers’ hand hygiene practices in HCFs in the GKMA.	Healthcare workers in selected HCFs and district leaders.	Key informant interviews	Facilitators of Hand hygiene among HCWs	i. Thematic content analysis
		Semi-structured interviews	Facilitators of Hand hygiene among HCWs	i. Thematic content analysis ii. Descriptive statistics
	Healthcare facilities	Observations	Facilitators of Hand hygiene among HCWs	i. Descriptive statistics
Explore the barriers for enhancing healthcare workers’ hand hygiene practices in HCFs in the GKMA.	Healthcare workers in selected HCFs.	Key informant interviews	Barriers of Hand hygiene among HCWs	i. Thematic content analysis
		Semi-structured interviews	Barriers of Hand hygiene among HCWs	i. Thematic content analysis ii. Descriptive statistics
	Healthcare facilities	Observations	Barriers of Hand hygiene among HCWs	i. Descriptive statistics
Determine the impact of mobile phone WASH messages and environmental cues on hand hygiene practice among health workers in HCFs in the GKMA.	Healthcare workers in selected HCFs.	i. Observations of healthcare workers ii. Laboratory analysis of hand rinsates for *E.coli*	i. Percentage change (increase or decrease) in the used hand hygiene opportunities ii. Percentage change (increase or decrease) in the number of E.coli colonies/100 ml of samples of hand rinsates	i. Use of statistical tests - McNemar test - Paired t-test - GEE Logistic regression

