**Fig. 1 Fig1:**
[figure not shown]
Study steps adapted from the Behaviour Centred Design model for behaviour change [30]

Prior to the implementation of the CRT, the investigators will obtain a list of HCFs and healthcare providers from the respective district health offices. This list will be used to randomly assign the clusters (HCFs) to the intervention and control groups. Once the clusters have been assigned, the study participants in the maternal and children’s wards within the selected HCFs will be informed about the purpose of the study and recruited in the study after the consenting process.

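### The GEE sentence misstates the correlation to be handled and does not name the health facility as grouping unit; with 15 facilities per arm, the variance method should be stated too

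*Protocol article*

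**What the plan says.** The quantitative part of the Data analysis section names a multivariable logistic GEE: "We shall run multivariable logistic regression under the generalised estimating equations (GEE) framework to account for the dependence of hand hygiene on the intervention". The sentence goes on to say that this is done marginally, and the next one promises population-average estimates adjusted for covariates. The Methods paragraph of the abstract gives the same reason for using GEE. On correlation the article says only: "An exchangeable correlation structure will be considered". It does not say within which unit.

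The rest of the article is clear about the cluster. Study design (text after Fig. 1): "This list will be used to randomly assign the clusters (HCFs) to the intervention and control groups". The randomisation text gives all HCWs of one HCF the same allocation. The sample-size text plans "15 HCFs under the intervention and 15 HCFs under the control arm) with 15 HCWs per HCF" and applies a design effect of 2.0 because HCWs are clustered in their facility. The GEE paragraph itself also promises a descriptive summary by facility: "We will calculate the prevalence of cluster level hand hygiene at baseline and follow-up for each HCF".

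The outcome section plans 20 opportunities per HCW and observation at baseline, midline and end-line. For the impact objective, Table 3 lists the McNemar test and the paired t-test beside the GEE.

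**The concern.** The stated reason for using GEE confuses the estimand with the nuisance correlation. The regression coefficient for arm describes how hand hygiene depends on the intervention. The grouping in a GEE exists for another purpose: to obtain valid standard errors when observations in the same HCF resemble each other.

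The data have four levels: opportunity, survey, HCW and HCF. An exchangeable structure could be set up within several of these, and the sentence that should settle the matter points elsewhere. Table 3 adds to the uncertainty. McNemar and paired t-tests compare the same people before and after, so as named they neither compare the arms nor allow for facility clustering.

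At stake are the false-positive rate and the interval width for the main result. How much depends on which reading an analyst adopts, so the readings have to be sized separately.

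**Working it through.** **Inputs from the article.** 15 HCFs per arm and 15 HCWs per HCF (30 × 15 = 450 HCWs); 20 opportunities per HCW (450 × 20 = 9000, as stated); two-sided 5% level with z = 1.96; control proportion 0.747; design effect 2.0. With 15 HCWs per HCF, the design effect implies an intracluster correlation (ICC) of (2.0 − 1)/(15 − 1) = 1/14 = 0.071. The article states no error rate for the GEE, so there is no such figure to reproduce. The planned total of 426 is not used below.

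**Assumptions.** Equal cluster sizes; arm-only model; HCF ICC 0.071 with a range of 0.03 to 0.15; where 20 opportunities per HCW are modelled, a within-HCW ICC of 0.10. The article gives neither the ICC range nor the within-HCW value.

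**Reading A: grouped by HCF, ordinary sandwich variance, normal reference.**

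1. The reference alone: the t critical value on 30 − 2 = 28 df is 2.048, not 1.96. P(|t28| > 1.96) = 6.0%.
2. The uncorrected sandwich divides each arm's between-HCF sum of squares by 15² where the unbiased form divides by 15 × 14. The variance is therefore too small by the factor 14/15.
3. Together: P(|t28| > 1.96 × √(14/15)) = P(|t28| > 1.894) = 6.9%.
4. If the software multiplies the variance by K/(K − 1) = 30/29: P(|t28| > 1.96 × √(14/15 × 30/29)) = P(|t28| > 1.926) = 6.4%.
5. Interval width against a Kauermann-Carroll variance with t on 28 df: 1.96/(2.048 × √(15/14)) = 0.924, about 8% narrower. Against the more conservative Mancl-DeRouen variance: 1.96/(2.048 × 15/14) = 0.893, about 11% narrower.

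**Reading B: grouped by HCW, so HCF clustering is ignored.**

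1. One outcome per HCW and the plan's design effect of 2.0: 2 × (1 − Φ(1.96/√2.0)) = 16.6%.
2. Twenty opportunities per HCW, with the ICC of 0.071 taken at the opportunity level: the variance of HCW means within an HCF is proportional to (1 − 0.071) × (0.10 + 0.90/20) = 0.135. The ICC of HCW means is 0.071/(0.071 + 0.135) = 0.347. The design effect on HCW means is 1 + 14 × 0.347 = 5.85, and 2 × (1 − Φ(1.96/√5.85)) = 41.8%.

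**Simulation under the null** (20,000 trials per setting, arm-only logistic GEE, proportion 0.747). The middle column is at ICC 0.071 and covers both outcome types unless stated.

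| Analysis | Type I error, ICC 0.071 | ICC 0.03–0.15 |
|---|---|---|
| HCF groups, uncorrected, z | 6.9% | 6.7–7.0% |
| HCF groups, K/(K − 1) factor, z | 6.4% | 6.3–6.5% |
| HCF groups, Kauermann-Carroll, t28 | 4.9–5.0% | 4.9–5.0% |
| HCF groups, Mancl-DeRouen, t28 | 4.2–4.3% | 4.2–4.3% |
| HCW groups, one outcome per HCW | 16% | 10–27% |
| HCW groups, 20 opportunities per HCW | 42% | 30–51% |

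The closed forms and the simulation agree. Under Reading A the error rate hardly moves with the ICC, because the number of clusters drives it. Under Reading B it depends strongly on the ICCs assumed.

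**The case against.** The strongest reply is that the article leaves little doubt about the cluster. Randomisation, the design effect and the planned facility-level prevalences all use the HCF, and the prevalence sentence stands in the same paragraph as the GEE. Read in full, the GEE sentence may be a loose way of saying that the intervention effect is modelled marginally, with correlation left to the sentence on the exchangeable structure. A bias-corrected variance and its degrees of freedom are also details that a journal article normally leaves to a statistical analysis plan, which is not shown.

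Most of this stands. A reader might infer that the trial will group by HCW and so ignore facility clustering. The documents do not support that: no sentence proposes it. Nor can one conclude that the intervals and p-values will be too optimistic, because the article neither specifies an uncorrected variance nor rules out a correction. Larger inflation from HCF-level covariates cannot be charged to the plan either, since it names no such covariates for this model. One might also object to an odds ratio as the effect measure, but a population-average odds ratio is a legitimate choice. Contrasting it with the planned difference requires reading the 25% and 5% increases as relative, which the article does not confirm.

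What the reply does not remove is that the reason given for GEE is wrong as written, appears in the abstract as well, and is not followed by any statement of the grouping unit. Table 3 may intend its paired tests for change within an arm, but it lists them for the impact objective without saying so.

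**Conclusion.** The point holds as a misstatement and an ambiguity in the analysis text. The GEE should be said to account for correlation of opportunities and HCWs within the randomised HCF, and the model text should name that unit.

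The numerical consequence is conditional. Under the natural reading, grouping by HCF, an ordinary sandwich variance with a normal reference would give about 6.5–7% type I error and intervals about 8% too narrow. That is mild. Serious inflation arises only if observations were grouped by HCW, which the article does not state: 16–17% at the plan's design effect of 2.0 with one outcome per HCW, and 30–51% with 20 opportunities per HCW under the assumed ICCs. The missing small-sample correction is not an error in itself. It belongs in the repair because 30 clusters are few enough for the choice to matter. The figures rest on equal cluster sizes and a model without covariates.

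**What to change.** - Reword the sentence in the Data analysis section, and its counterpart in the abstract, so that GEE accounts for correlation of observations within the randomised HCF.
- Specify the model as grouped by HCF with an exchangeable working correlation, committed to and not merely considered.
- State a bias-corrected robust variance, for example Kauermann-Carroll or Fay-Graubard, with a t reference on 28 degrees of freedom less one for each HCF-level covariate.
- State that the McNemar and paired t-tests in Table 3 are not used for the between-arm effect.

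The cost is a few sentences and a few lines of code. Intervals become slightly wider: relative to uncorrected ones, 1/0.924 = 1.08, so about 8% with the Kauermann-Carroll form. No change to the design or data collection is needed. Reporting a risk difference beside the odds ratio is optional and not part of this correction.

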Secondly, hand rinsates from HCWs participating in the CRT will be collected immediately after the hand hygiene observations during baseline and end-line. The samples (hand rinsates) will be collected by a team of trained environmental health officers. During sampling of hand rinsates, HCWs will put their hands, one at a time in Whirl-Pak bags containing distilled water. The HCWs will wash their hands by rubbing the inner hands for about 2 min and the enumerator massaging their hands from outside the whirl pak bag to remove any potential pathogens. Aseptic techniques will be used to collect duplicate samples from each of the study participants (HCWs) during baseline, midline and end-line. The samples will be stored in sterile plastic bottles and transported on ice to the laboratory for further analysis within 4 h. The hand rinsates will be analysed for *Escherichia coli (E.coli)*, to establish if there are differences in the levels of contamination on the hands of the HCWs before and after the intervention. During analysis, hand rinsates will be diluted using the ratios of 1:1, 1:10 and 1:100. The membrane filtration method (with Chromocult agar) will be used to concentrate samples, and incubation will be done at 37 °C for 24 h. Colonies of *E.coli* will be identified by their dark blue to violet colour, and they will be counted and recorded per 100 ml of sample.

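### Table 3 sets the E. coli indicator as a percentage change with no stated unit, and no listed test compares E. coli concentration between the randomized arms with clustering

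*Protocol article*

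**What the plan says.** The Outcome measurement section defines the laboratory outcome as a concentration: "The secondary outcome will be *E. coli* concentration levels in hand rinsates from HCWs, which indicates recent fecal contamination and hand hygiene failure". Of the colonies it says that "they will be counted and recorded per 100 ml of sample". The stated purpose of the assay is a before/after one: "to establish if there are differences in the levels of contamination on the hands of the HCWs before and after the intervention".

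Table 3, under objective 3 (the impact of the intervention), gives a different derived quantity: "Percentage change (increase or decrease) in the number of E.coli colonies/100 ml of samples of hand rinsates". No unit of calculation is given, and no rule for zero counts. One list of methods serves both indicators of that objective: "Use of statistical tests - McNemar test - Paired t-test - GEE Logistic regression".

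The text under Quantitative analysis names one model: "We shall run multivariable logistic regression under the generalised estimating equations (GEE) framework". It links that model to hand hygiene. No model is named for E. coli.

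**The concern.** Two things do not fit together.

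First, objective 3 asks for the effect of an intervention allocated to 30 facilities, 15 per arm. That needs a comparison of arms that respects facilities as the randomized units. None of the three listed methods does this for a concentration.

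Second, percentage change behaves very differently according to where it is calculated. A colony count can be zero, and a change relative to zero has no value. A fall cannot go below -100%, while a rise has no ceiling: from 1 to 10 colonies is 100 x (10 - 1)/1 = +900%. An average of individual percentages can therefore point the wrong way.

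E. coli is the trial's only laboratory outcome. The article's limitations section expects social desirability bias in the observed primary outcome, so the laboratory result is the main check on it.

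**Working it through.** The article gives no mean, SD, zero fraction or power for E. coli, so there is no figure of the plan's own to reproduce.

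**Step 1. Match each listed test to the concentration.**

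| Listed method | Outcome it takes | Compares arms? | Allows for clustering by facility? |
|---|---|---|---|
| McNemar | paired binary | no | no |
| Paired t-test | paired continuous | no, before/after only | no |
| GEE logistic | binary | yes | yes |

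The only between-arm method needs a yes/no outcome, and the article gives no E. coli cut-off. This result does not depend on how the percentage change is calculated.

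**Step 2. Zero baselines, if the change is taken per HCW.** The formula is 100 x (end-line - baseline)/baseline, undefined at baseline 0. The planned sample is 450 HCWs. The zero share is an assumption: at 10%, 25% and 50% zeros, about 45, 112 and 225 HCWs have no value.

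**Step 3. Mean of individual changes against change of arm means.** Counts were simulated with no true change (control) and with a true halving (intervention). Every distribution is assumed.

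Negative binomial counts, baseline and end-line independent:

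| Mean, dispersion | Zero baselines | Per-HCW mean, no change | Per-HCW mean, halved | Arm means, no change | Arm means, halved |
|---|---|---|---|---|---|
| 2, 0.3 | 54% | -0.3% | -50.0% | 0.0% | -50.2% |
| 10, 0.3 | 35% | +190.7% | +47.0% | +0.7% | -49.6% |
| 10, 0.5 | 22% | +174.5% | +37.6% | -0.5% | -50.2% |
| 50, 0.3 | 22% | +722.6% | +318.0% | -0.2% | -50.3% |

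Poisson-lognormal counts, half of the log-variance between persons:

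| Log-mean, log-SD | Zero baselines | Per-HCW mean, no change | Per-HCW mean, halved |
|---|---|---|---|
| 0, 2 | 41% | +146% | +30% |
| 1, 2 | 26% | +270% | +86% |
| 2, 2 | 14% | +390% | +148% |
| 3, 1.5 | 3% | +213% | +58% |

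The lognormal figures move by a few points between simulation runs. The change of arm means stayed within about 2 points of the truth there too.

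**Step 4. Why the sign flips.** Halving the end-line mean at every baseline value halves the mean of end-line/baseline. If the per-HCW mean change is c% with no effect, it is (100 + c)/2 - 100 under a halving. With c = 190.7 this gives 290.7/2 - 100 = +45%, against +47.0% simulated. The result is positive whenever c exceeds 100, which held in seven of the eight settings. The exception is the negative binomial with mean 2.

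**The case against.** The strongest reply is that the per-HCW calculation is not in the document. Table 3 speaks of samples in the plural. Its companion indicator for hand hygiene reads naturally as a group summary, and the analysis text plans cluster-level hand hygiene prevalence for each facility. At arm or facility level the percentage change is defined whenever the baseline mean is above zero, and Step 3 shows that at arm level it is sound. That stands: the distortion is a consequence of one reading, not of a stated procedure. The other reading is also open, since rinsates are taken from each participant and two of the three listed tests are paired. That is why the unit has to be stated.

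A reader might go further and infer that the secondary outcome cannot be derived at all. The documents do not support this. The outcome is defined as a concentration and recorded per 100 ml, so it exists for every sample, zero included. Nor does the article say that E. coli will be dichotomized; its phrase about hand hygiene failure interprets the marker.

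It can also be said that an analysis plan not shown may name the model and the zero rule. That would excuse silence. Here Table 3 does name the indicator and the methods, and the named methods do not answer objective 3 for this outcome.

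Finally, even the per-HCW version keeps the order of the arms: (100 + 47.0)/(100 + 190.7) = 0.51, close to the true ratio of one half. That is correct, but no listed method makes this comparison, and a before/after reading within the intervention arm would show an average increase.

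**Conclusion.** The point holds in two parts of different strength. That no listed method compares E. coli concentration between arms with clustering follows from the text of Table 3 and the analysis section and needs no assumption. That the unstated unit can mislead is conditional. If individual percentages are averaged, HCWs with a zero baseline drop out, and under a true halving the mean change came out between about +30% and +318% in seven of eight assumed settings and at -50% in the eighth. If arm means are used, the problem does not arise. How often zeros will occur in this trial is unknown, so the figures show what can happen and do not forecast it. The measurement itself is sound; the indicator and its listed tests should be revised.

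**What to change.** In Table 3 and under Quantitative analysis:

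- State the E. coli effect as a between-arm ratio of mean colonies per 100 ml at follow-up, from a GEE count model (negative binomial or log link) clustered by facility and adjusted for the HCW's baseline result. Zero counts then need no special rule.
- As a supporting analysis, put E. coli detected versus not detected into the GEE logistic model already planned, and state that definition.
- Keep percentage change only as a descriptive summary calculated on arm or facility means, not averaged over individual HCWs.

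The cost is wording and a little analysis work. The baseline results are already planned. The main effect would be reported as a ratio, and the supporting one as an odds ratio, in place of a percentage change.
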